## Abstract

**Background:**

Self-management support is increasingly viewed as an integral part of chronic condition management in adolescence. It is well recognized that markers of chronic illness control deteriorate during adolescence. Due to the increasing prevalence of long-term chronic health conditions in childhood and improved survival rates of previously life-limiting conditions in children and adolescents, significant numbers of adolescents are having to manage their chronic condition effectively as they transition to adult health care. Therapy adherence has been identified as a major challenge for young people living with a chronic condition such as cystic fibrosis, diabetes, or asthma requiring long-term pharmacological therapy and/or lifestyle modifications. Most systematic reviews on self-management interventions address adult populations. Very few intervention studies are directed at adolescents with a chronic condition who are transitioning to adult health services. This protocol describes a prospective randomized controlled trial of a standardized self-management intervention program delivered to adolescents aged 15–18 years prior to their transfer to adult care. This study has been designed to provide evidence regarding self-management programs for adolescents and is the first study to use the Flinders Program with this important, under-researched age group.

**Methods:**

A randomized controlled trial is used to investigate the effectiveness of a modified adolescent-friendly version of an adult self-management program. This program is directed at improving self-management in an adolescent cohort 15–18 years of age with a chronic condition being treated in a specialist pediatric hospital. Participants will be randomized to either usual care or the modified Flinders Program plus usual care. Data collection will include measures of specific illness control, unscheduled hospital admissions, and questionnaires to record self-management competencies, quality of life, self-efficacy, and outcome measures specific to the chronic condition at baseline, 3 months, 6 months, and 12 months after delivery.

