^*^Sustained improvement in measure of disease control over a 12-month period from baseline

**Table 2 Tab2:** Schedule of enrolments, interventions, and assessments

Procedure												
**Measure**	**Baseline**		**3 months**		**6 months**		**9 months**		**12 months**		**18 months**	
	**I**	**C**	**I**	**C**	**I**	**C**	**I**	**C**	**I**	**C**	**I**	**C**
Informed consent	**X**	**X**										
Demographic data collection	**X**	**X**										
Measures of illness control	**X**	**X**	**X**		**X**	**X**		**X**	**X**	**X**		**X**
Unplanned hospital visits	**X**	**X**	**X**		**X**	**X**		**X**	**X**	**X**		**X**
Questionnaires	**X**	**X**	**X**			**X**		**X**	**X**			**X**
Partners in Health (PIH) Scale	**X**	**X**	**X**		**X**	**X**		**X**	**X**	**X**		**X**
Feasibility and Acceptability Questionnaire (FAQ)									**X**			**X**
Flinders Program delivery	**X**		**X**		**X**	**X**	**X**	**X**	**X**	**X**		**X**
Booster session					**X**					**X**		

***I*** Intervention (Flinders Program plus usual care), ***C*** Control (waitlist plus usual care)

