#### Follow-up data collection

Adherence to prescribed treatment regimenBaseline observations will be collected from both the waitlist control group and the intervention group before randomization. Potential participants in the intervention group will be contacted via phone by a member of the research team. Follow-up of participants in the intervention group will be undertaken by a member of the research team via phone or telehealth (depending on the young person’s preference) at 3, 6, and 12 months to follow-up on adherence to the prescribed treatment post intervention. Participants who do not respond to 3 attempts to contact them at any time point will be treated as missing data.

Information from the participants will be obtained by completing the PIH scale via a semi-structured interview. Subsequently, participants allocated to the wait list control group will be contacted by phone by a member of the research team and provided with a self-management information brochure, with no further contact from the research team. At 6 months, participants in the waitlist control group will be contacted by phone by a member of the research team and invited to participate in the intervention as described for the initial intervention group.(b)Markers of illness control and unplanned hospital visits

The research team will obtain standard measures of illness control for all participants who have been recruited into the study and who have consented to clinical information being obtained for research purposes. The control of chronic illness is the best quantitative measure of therapy adherence that is available. This will be undertaken by way of the research team extracting information from the electronic medical records (EMR) and the young person’s primary physician contacted for further information. Data on unplanned hospital visits will be retrieved by the research team from EMR and/or accessed through the young person’s My Health Record if available.

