#### Measures of illness control

To clarify our primary outcome measure, we provide here a list (not exhaustive) of the more common conditions seen in specialist care in pediatric hospitals which require significant self-management. These include diabetes, other chronic endocrine conditions, asthma, cystic fibrosis, epilepsy, inflammatory bowel disease, haemoglobinopathies, and inherited metabolic disorders [49]. Measures of illness control can be described as a quantitative measurable parameter including laboratory measurement that can be used to identify clinically meaningful endpoints that can be used to assess the status of a known disease. Common features of chronic conditions include prolonged duration, absence of spontaneous resolution, and a lack of curative therapy, requiring ongoing long-term lifestyle modifications and/or pharmacological treatment to be taken consistently and regularly. These characteristics define the chronicity of each of the conditions that will be assessed as part of the study [50]. An improvement of illness control based on clinical experience, given empirical data are lacking, will be assessed by utilizing predetermined measures of illness control, previously developed in conjunction with specialist teams [51] (Table 1). The proportion in each group who achieve improvement in illness control will be described by number and percentage and the difference expressed as relative risk and confidence interval. Measures of effect will be expressed as relative risk with a decrease of 10% from baseline to 12 months. For any conditions not appearing on this list, we will consult with the referring specialist team to determine the appropriate measure of illness control and what would be clinically considered as an improvement of that particular chronic condition. Improvement of illness control will be defined as sustained improvement in measure of disease control over a 12-month period from baseline as defined in Table 1. Illness control will be defined using a binary notation of which a “yes” or “no” answer will be provided, defined as achieving improvement or not. In many conditions, there will be more than one quantitative measure of illness control. For the purposes of outcome analysis, we have selected the most clinically important marker, but will have data on secondary markers of illness control where relevant.

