#### Secondary outcome measures

The secondary outcome measures are the number of unplanned or unscheduled health care emergency department visits, quality of life, self-efficacy, time management, health-related distress, and feasibility and acceptability of a modified self-management program designed for adolescents with a chronic condition which include:

- Hospital admissions and emergency department visits due to chronic illness will be obtained from the medical records or My Health Record system if the young person is registered. An unplanned hospital admission is defined as an admission that is not part of routine illness management, not from an admission waiting list and which can be associated with a deterioration of illness control as a result of insufficient self-management practices [51]. These measures will be collected in all study participants at baseline in both standard care and intervention groups as with other measures except the feasibility and acceptability questionnaire at interval periods of 3, 6, and 12 months from baseline. The median and range of numbers of unplanned hospital admissions per person in each group will be described.

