#### Partners in Health (PIH) scale

The primary outcome is to determine the effectiveness of using a modified version of the Flinders Program™ as measured by illness control and unscheduled hospital admission as described above. Improvements in self-management will be measured using the validated PIH scale which is incorporated in the Flinders Program™ and provides a formal, low burden scale (usually takes less than 10 min to complete) designed specifically to measure improvements in self-management behaviors and health outcomes over time [46].

The PIH scale assesses self-management capacity using a validated Likert self-rated scale (0 being very little to 8 a lot) for each of the 12 questions covering the principles of self-management including knowledge and treatment of the condition (Q1 and 2); engagement with health care providers (Q3 and 4); access to services (Q5 and 6), monitoring and responding to signs and symptoms (Q7 and 8); physical, social, and emotional impacts of living with a chronic illness (Q9, 10, and 11) and lifestyle risk factors (Q12) [52, 53]. Questionnaires will be completed by all participants independently at commencement of the study as detailed in the study timeline. Scores of less than or equal to 4 are flagged by the health professionals as areas to be addressed. The PIH Scale demonstrates high internal consistency (0.81) and construct validity with a 4-factor analysis for knowledge, symptom management, adherence, and coping accounting for 80% of the variance [54]. The number and percentage of each randomized group who have a score of less than or equal to 4 will be collected at each timepoint 3, 6, and 12 months from baseline.

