#### Kessler Psychological Distress Scale (K10)

The Kessler Psychological Distress Scale (K10) is a well-recognized instrument which has demonstrated content and construct validity for measuring non-specific symptoms of psychological distress including behavioral, emotional, cognitive, and psychophysiological manifestations [62]. Initially developed for the US National Health Interview Survey (NHIS), the 10-item scale (K10) has been extensively used in both clinical and general populations including adolescents, and used in a variety of cultural and sociodemographic backgrounds [63]. The K10 scale measures the frequency of symptoms (nervousness, hopelessness, sadness, worthlessness, and fatigue) experienced in the past month using a 5-point Likert scale ranging from none of the time (1) to all of the time (5), producing a total score range of 10–50 with higher scores correlating to more distress [62]. A study conducted by Sampasa-Kanyinga et al. found that the K10 scale has satisfactory psychometric properties for use as a measure of non-specific psychological distress with high internal consistency (0.84) [64].

Adolescents with a chronic condition are more likely to develop psychiatric and behavioral disorders including depression and low self-esteem than their healthy counterparts. Thus, the K10 scale was chosen as it presents as a useful tool in identifying psychological symptoms in participants, and from our previous clinical experience in working with adolescent populations, the accessibility and simplicity of the K10 scale makes it an ideal instrument to use within this population group. [65]. It is not a diagnostic tool.

The mean and standard deviation of the scores for the outcome measures described above will be described in each group and at each time point, following randomization at baseline, 3 months, and 12 months.

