## Statistical methods

### Statistical methods for primary and secondary outcomes {20a}

Participant demographic, clinical characteristics, and study outcomes will be presented using standard descriptive statistics, including mean, standard deviation and range or median, quartiles and range for continuous variables, frequencies and percentages for categorical variables, and the Kaplan–Meier method for time to event variables. All statistical analyses will use the intention to treat principle whereby participants are analyzed in their randomized groups, regardless of treatment received. The primary outcome of the number of responses in each treatment arm will be compared using a chi-square test and the difference in proportions presented with a 95% confidence interval. Other study outcomes will be compared between randomized groups using standard tests, including chi-square tests for categorical outcomes, two-sample *t*-tests or nonparametric equivalent for continuous outcomes, Poisson regression models for count data, and log-rank test for time-to-event data. For longitudinal outcomes, statistical models that account for the correlation between repeated observations in the same participant will be used. A more detailed pre-specified statistical analysis plan is forthcoming with completion of the trial and will be made publicly available.

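### Follow-up is counted from delivery, baseline or randomization in different places, and Table 2 leaves the arms with no post-baseline questionnaire month in common

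*Protocol article*

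**What the plan says.** The protocol article gives three origins for the follow-up clock.

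- **Delivery of the programme.** The Abstract (Methods) has "outcome measures specific to the chronic condition at baseline, 3 months, 6 months, and 12 months after delivery". Follow-up data collection describes contact with the intervention arm "at 3, 6, and 12 months to follow-up on adherence to the prescribed treatment post intervention".
- **Baseline.** Measures of illness control defines the primary outcome as "sustained improvement in measure of disease control over a 12-month period from baseline as defined in Table 1", and the Table 1 footnote agrees. Secondary outcome measures has both groups measured "at interval periods of 3, 6, and 12 months from baseline". The Partners in Health (PIH) section says the share of each randomized group with low scores "will be collected at each timepoint 3, 6, and 12 months from baseline".
- **Randomization.** The closing paragraph of the K10 section promises means and standard deviations in each group "following randomization at baseline, 3 months, and 12 months". Plans for assessment and collection of outcomes {18a} lists the quality-of-life, time-management and distress questionnaires at baseline, 3 and 12 months of follow-up, without naming an origin.

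Trial design {8} has controls wait six months before they start the programme. Table 2 uses one set of month columns for both arms, with programme delivery beginning at baseline in the intervention arm and at month 6 in the control arm. Under Statistical methods {20a}, "participants are analyzed in their randomized groups, regardless of treatment received".

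**The concern.** For an intervention participant who starts on time, the three origins nearly coincide. For a control, delivery comes six months after randomization, so the choice of origin decides when the control is measured and how much of the programme the control has already had.

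A randomized comparison needs both arms measured at the same time since randomization. If the control schedule follows the control arm's own start, values labelled 3 months or 12 months in the two arms are not contemporaneous. The outcomes most exposed are quality of life, time management and distress, which belong to the second study hypothesis in Objectives and hypothesis {7}. An analyst following the Abstract, one following the K10 section and one following Table 2 would each build a different dataset. Self-reported questionnaires not collected at the right month cannot be recovered at analysis.

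**Working it through.** **Sample size, for completeness.** The plan states 27 per group for 15% against 50%, 80% power and two-sided 5%. With the pooled-variance formula, n = [1.960 × √(2 × 0.325 × 0.675) + 0.842 × √(0.15 × 0.85 + 0.50 × 0.50)]² / 0.35² = 26.9, so 27. The stated figure reproduces (power 80.2%), and the timing question does not alter it.

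**Clock conversion.** Months since own start = study month minus the delay to the first session (0 in the intervention arm, 6 in the control arm). For controls: 6 − 6 = 0; 9 − 6 = 3; 12 − 6 = 6; 18 − 6 = 12.

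**Table 2, row by row (study months):**

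| Row | Intervention | Control | Control, months after own start | Shared post-baseline months |
|---|---|---|---|---|
| Illness markers, unplanned visits, PIH | 0, 3, 6, 12 | 0, 6, 9, 12, 18 | 0, 3, 6, 12 | 6 and 12 |
| Questionnaires | 0, 3, 12 | 0, 6, 9, 18 | 0, 3, 12 | none |
| Booster session | 6 | 12 | 6 | – |
| Feasibility questionnaire | 12 | 18 | 12 | – |

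In every row, the control months after baseline are the intervention months shifted by six. The control schedule therefore follows the control arm's own delivery.

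**Consequence 1: month 3.** No row has a control mark at month 3. Secondary outcome measures and the PIH section both call for both groups at 3 months from baseline.

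**Consequence 2: questionnaires.** The K10 section needs both groups at months 3 and 12 after randomization. Controls have no Questionnaires mark at either. The control values that carry the same label on the delivery clock are:

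- 3 months: intervention month 3 against control month 3 + 6 = 9, after 9 − 6 = 3 months of programme;
- 12 months: intervention month 12 against control month 12 + 6 = 18, after 18 − 6 = 12 months of programme.

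The nearest other pairings (intervention 3 with control 6; intervention 12 with control 9) are still three months apart, and neither gives the same month in both arms.

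**Consequence 3: the primary marker.** It has marks in both arms at months 6 and 12, its definition counts from baseline, and Follow-up data collection takes it from medical records for all recruited participants who consented. A same-month comparison is available. Only month 3 lacks a control entry.

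**The case against.** The strongest reply is that the Abstract phrase is loose wording. The operative definitions, including the primary outcome, count from baseline; randomization and baseline are practically adjacent; and the post-intervention wording concerns only the intervention arm, where delivery starts at baseline. All of that stands for the primary marker. It does not explain the control columns of Table 2, which are a data-collection schedule.

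A second reply is that the longitudinal models foreshadowed in Statistical methods {20a} could handle unequal months. A model could interpolate, but the result would rest on an assumed trajectory through a change of exposure at month 6. It would not supply the observed group means that the K10 section promises.

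Two stronger readings are tempting, and the documents do not support them.

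- A reader might infer that participants who never start have no follow-up date, drop out of the comparison and so tilt the result towards the programme. The protocol extracts markers from records for all recruited participants, allows the outcomes of withdrawn participants to be taken from records, and analyses everyone as randomized. It gives no non-start rate from which a bias could be sized. On a delivery clock controls would also have had the programme, which pulls the difference towards nil rather than in the programme's favour.
- A reader might infer that the 12-month primary value in controls is really a month-18 value. Table 2 marks controls at month 12 as well; month 18 is additional.

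**Conclusion.** The concern holds for the wording of the clock and for the Table 2 schedule, with its main effect on the secondary questionnaire outcomes. Controls have no month-3 assessment of any outcome measure, and the arms share no post-baseline questionnaire month. The promised questionnaire comparison at 3 and 12 months cannot be produced as scheduled, except by using control values taken six months later and after 3 and 12 months of programme respectively. The primary marker is affected little, and no bias in favour of the programme is claimed.

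This rests on reading the Table 2 columns as study months common to both arms, which the month-6 start of control delivery and the month-12 control booster support. It should be corrected, because the missing questionnaires cannot be reconstructed later. That controls have had about six months of programme by month 12 is a separate design issue, which this point neither decides nor resolves.

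**What to change.** 1. State one origin, the date of randomization, for every between-arm assessment. Align the Abstract, Follow-up data collection, Secondary outcome measures, the PIH section, the K10 section, {18a} and Table 2 with it. Say that baseline adjoins randomization, and reconcile its order: Follow-up data collection places it before randomization, Sequence generation {16a} after.
2. Extract illness markers and unplanned visits at months 3, 6 and 12 after randomization for everyone randomized, including those who never start.
3. Add control questionnaires at the post-randomization months used in the intervention arm, at least months 3 and 12. Add the PIH scale for controls at month 3, since its section calls for it.
4. Keep time since delivery for within-arm description only.

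**Cost.** The record-based outcomes need no visits. The questionnaires mean a few short extra control collections, and the one at month 3 needs an exception to the rule in Follow-up data collection that the research team does not contact controls again before month 6. Standard care procedures already includes one scheduling call in that period. Some programme sessions will no longer fall on an assessment date.

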**Discussion:**

This study will provide a better understanding of the elements required for effective self-management programs in adolescents with a chronic condition and address some important knowledge gaps in current literature. The study will be carried out in collaboration with the Discipline of Behavioural Health at Flinders University, Adelaide, Australia, in order to inform the development of an adolescent version of the successful and validated Flinders Program™.

**Trial registration:**

Australian and New Zealand Clinical Trials Registry (ACTRN12621000390886). Registered on April 8, 2021.

**Supplementary Information:**

The online version contains supplementary material available at 10.1186/s13063-022-06740-9.

## Administrative information

Note: The numbers in curly brackets in this protocol refer to the SPIRIT checklist item numbers. The order of the items has been modified to group similar items (see http://www.equator-network.org/reporting-guidelines/spirit-2013-statement-defining-standard-protocol-items-for-clinical-trials/).

## Introduction

### Background and rationale {6a}

The concept of supporting self-management skills in those with a physical chronic condition has been recognized globally as an important health strategy in dealing with the growing burden of non-communicable disease (NCD), and the associated treatment costs of living with a chronic condition [1]. Advances in medical technology and medical treatments have led to improved survival rates across a range of chronic conditions [2]. As a result, the number of adolescents living with a chronic condition and disability has been steadily increasing in Australia and internationally [2, 3]. In 2009, there were nearly four million young people aged 12–24 years residing in Australia. This number is projected to increase to 4.8 million by 2038 [4]. According to the Australian Institute of Health and Welfare (AIHW) between 2007 and 2008, an estimated 60% of young people aged 12–24 years had a chronic condition. While a very broad definition was used, on current data at least 10% of these will have a longstanding chronic condition requiring significant self-management skills. Supporting the development of self-management skills has been well recognized in adults as an important health strategy for dealing with the burden of chronic illness. However, little is known about the effectiveness of self-management support programs for adolescents who are in the process of developing autonomous self-management skills [5].

Adolescence is characterized by rapid emotional, physical, psychosocial, and cognitive change as adolescents make the transition from childhood to young adulthood. In addition to the normal developmental challenges faced by all adolescents [2], young people with a chronic illness have the additional burden of managing their chronic condition along with its associated and often complex behaviors which the young person is expected to incorporate into their everyday life. These behaviors include regularly taking prescribed medications, monitoring symptoms, using medical devices, and lifestyle changes including nutrition and/or physical activity [6–10]. This therapy burden together with the often significant impact of a chronic illness on the young person’s physical, psychosocial, and even neurocognitive development often leads to non-adherence to treatment regimens [11–13]. Non-adherence is viewed as likely more challenging for young people than any other age group [7–9, 14–16]. The terms compliance, adherence, and concordance have been used interchangeably in the literature and are often used to describe self-management behaviors with notable differences between the terminology. Compliance is defined as “The extent to which the patient’s behavior matches the prescribers recommendations” [17]. However, its use is declining as it seems to imply lack of involvement by the patient. Adherence is defined as “the extent to which the patient’s behavior matches agreed recommendations from the prescriber” [13, 17, 18]. Concordance focuses on a collaborative agreement between the clinician and the young person about their treatment regimen, which supports components which are required for long-term management of their chronic condition with the emphasis on a collaborative partnership [18]. This aligns well with the principles of self-management.

The concept of self-management encompasses a combination of different strategies directed towards improving knowledge of their chronic condition together with the cognitive behavioral strategies which are required for long-term behavior change leading to improved health outcomes [19–22]. Studies in both adults and younger children with a chronic condition have demonstrated that combining self-management with medical treatment leads to improved health outcomes and better quality of life than prescriptive medical management alone [23].

Self-management has been defined as the actions undertaken by the individual on a daily basis to effectively manage their chronic condition and the associated impact of living with a chronic illness [24, 25]. The concept of promoting self-management skills involves much more than just providing didactic patient education alone. Rather, the young person is provided with skills that improve active management of their chronic condition. These include navigating the health care system, making independent decisions about their treatment, action planning, and developing self-efficacy and problems solving skills which can be applied to everyday situations [10, 19, 20, 26, 27]. Self-management support is the encouragement provided by health professionals, relatives, and significant others to increase the adolescent’s skills and confidence in managing their chronic condition [24, 25, 28–30]. Self-management is necessary for an effective transition to adult care, which is more than just a “transfer event” from pediatric to adult services. Rather it involves a process whereby adolescents develop the skills to carry out daily health care tasks independently in preparation for the transfer to adult services [31].

To date, there has been little attention directed towards the development of self-management in young people with a chronic illness, with the majority of research focusing on the adult population [7, 32, 33]. A study by Mammen and colleagues found that greater self-efficacy was demonstrated when self-management programs are precisely directed at the unique developmental needs of adolescents [34]. Adult models often overlook the developmental needs of young people which make it difficult to simply adapt these approaches to adolescents [10]. The overall goal of self-management programs is to provide a conceptual framework in which to deliver information and training and promote skills development, practical tools, and resources to improve self-efficacy and medical management, thereby improving the health outcomes of individuals living with a chronic condition [5, 10, 35]. Failure to effectively develop self-management skills in adolescence also has the potential to adversely influence future health trajectories in later life [15].

Managing a chronic condition and adapting behavior changes involves a collaborative approach between the young person and health care providers to enable more effective management of their chronic condition resulting in improved health outcomes [28]. It is this concept that drives the Flinders Program™ which is used in this study. From our experience, adolescents respond well to the Flinders Program™ in a clinical setting [36]. This study describes a prospective randomized controlled trial comparing a standardized self-management intervention program with usual care delivered to adolescents aged 15–18 years prior to their transfer to adult care and is the first study to use the Flinders Program™ with this important and under-researched age group.

